### Recruitment {15}

The trial poster will be displayed in fertility clinics and on the fertility pages of local trust websites for the purpose of advertising the trial. Trial information will also be given out at information evenings. Where suitable, Patient Identification Centres (PIC) will be utilised to identify patients referred to participating fertility clinics from secondary care fertility clinics.

## Assignment of interventions: allocation

### Sequence generation {16a}

Sequence generation for randomisation will be done using a secure web-based randomisation system immediately prior to randomisation and subsequent allocation of intervention.

The randomisation will be stratified by a fertility clinic and minimised by the following:
Participant’s age (< 35 years, 35–40 years, > 40 years)Type of planned first embryo transfer (fresh, frozen).

Minimisation for both factors will include a 90% weighting to introduce 0.9 as a stochastic factor for allocation probability.

### Concealment mechanism {16b}

The allocation sequence will be implemented using a secure web-based randomisation system. The system will be tested prior to deployment using dummy sequences.

Access to the live randomisation system is given only to embryologists, who are the only staff unblinded to the intervention. Each embryologist at centres uses a personal, unique login and password to access the randomisation system. User access and allocation of the correct level of access is managed by the central trial team. Introduction of weighting of minimisation factors (as described above) will introduce a stochastic element that ensures allocation sequences remain unpredictable.

### Implementation {16c}

A secure web-based randomisation system will generate the allocation sequence. Randomisation will be performed on the day of fertilisation check. Participants satisfying all the eligibility criteria for the trial will be randomised into one of the three treatment arms in a 1:1:1 ratio.
Time-lapse imagingUndisturbed cultureStandard treatment

Randomisation will be done by a trained and delegated embryologist member of the study team using a secure web-based randomisation system hosted by epiGenesys, University of Sheffield, which is accessible around the clock, 365 days of the year. Back-up procedures in case of technical issues with accessing the randomisation system will be made available and described in a study-specific standard operating procedure (SOP).

## Assignment of interventions: blinding

### Who will be blinded {17a}

It will not be possible to blind embryologists to the intervention. The trial statistician is ‘semi-blinded’ to the allocation—they will see data by trial arms for DMC report generation, but trial arms will not be identified. All other local and central trial staff, including clinicians performing the embryo transfer and data analysts, will be blinded. Participants will be blinded to the allocated intervention until the end of their participation in the trial. This will either be a negative pregnancy test which is approximately 2 weeks after embryo transfer or the end of their pregnancy. Once randomisation is performed, embryologists will document the allocation in a local randomisation form that will remain in the lab to prevent unblinding and proceed with the intervention and laboratory procedures described below. A randomisation log will be kept in the lab and accessed and updated by study embryologists only.

### Procedure for unblinding if needed {17b}

Local delegated embryologists will be the holders of the code break list for each site. Given the low risk of the intervention, it is unlikely that urgent unblinding should be required to guide patient management. In the unlikely event that an emergency codebreak is requested, the PI or healthcare professional will request unblinding from the embryologist. On receipt of the treatment allocation details, the PI or treating healthcare professional will continue to deal with the participant’s medical emergency as appropriate. The PI must document the breaking of the code and the reasons for doing so on the CRF/data collection tool, in the site file and medical notes.

Additionally, participants may request to be informed of their allocation when they reach the end of their study participation (either due to unsuccessful pregnancy or end of pregnancy). Care will be taken not to disclose the allocation to any other member of the research team.

Any unblinding, including accidental unblinding (which constitutes a protocol deviation), will be reported to the Data Monitoring Committee (DMC) and included in the final study report.

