### Trial design {8}

#### Study design

The trial is a pragmatic, multi-centre, three-arm parallel-group randomised controlled trial using re-randomisation.

The hypothesised benefit of the TLI systems may be due to either a closed undisturbed culture system or the use of morphokinetic parameters for embryo selection or both. Hence, a three-arm study design is necessary to answer the research question and define the contributions of both the variables involved.

The trial will compare the results of the following:
Intervention 1: incubation and assessment of embryos using TLI systems (morphokinetic parameters + undisturbed culture + morphological assessment)Intervention 2: incubation of embryos in undisturbed culture and standard embryo assessment (undisturbed culture + morphological assessment)Control: standard care (morphological assessment alone)

The design of this trial will be pragmatic. It will allow centres to use a TLI system of their choice. The trial tests the basic premise that undisturbed culture and/or addition of morphokinetic parameters to standard embryo assessment improves outcomes in IVF/ICSI treatment. It does not aim to test nor validate individual TLI systems and algorithms. The trial will use the manufacturer’s algorithm for morphokinetic parameters as a minimum standard to ensure quality control and external validity to the study. It will allow centres to develop more sophisticated centre-specific algorithms by incorporating further parameters into the basic model recommended by the manufacturer. It is accepted that clinical protocols for IVF and laboratory conditions will vary with each centre. All clinical and laboratory elements of IVF/ICSI treatment apart from the randomised intervention will be carried out according to local centre protocols, ensuring only that there is no variation across the three study arms in culture medium and incubator settings (temperature, CO_2_ and O_2_ levels) within each centre.

Couples having IVF/ICSI treatment will be eligible for the trial. Eligible participants will be screened in the fertility clinics and invited to participate in the trial. Following informed consent from both partners, participants will be randomised in a 1:1:1 ratio to one of the three arms: TLI, undisturbed culture or standard care. Women will be followed up until either a negative pregnancy test 2 weeks after embryo transfer or to the end of their pregnancy following a positive pregnancy test.

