### Participant timeline {13}

The trial intervention will be an alternative method for incubation and assessment of embryos created during IVF/ICSI. There will be no extra added intervention for the embryos. There will be no extra visits/intervention for the participants (Table 1).

**Table 1 Tab1:** Schedule of assessments

	Baseline	Day of egg collection (D0)	Day of fertilisation check (D1)	Days 3, 5 and optionally day 6	Routine visit to fertility unit approx. 2 weeks after embryo transfer	Approx. 8 weeks of gestation	Approx. 24 weeks of gestation	Approx. 6 weeks after the expected due date
Informed consent	X							
Confirmation of informed consent		X						
Baseline demographic and clinical data	X							
Randomisation and confirmation to randomised participants			X					
Ineligible consented participants informed			X					
Embryo grading; transfer if appropriate				X				
Documentation of morphokinetic parameters (arm 1 only)				X				
Pregnancy test outcome					X			
Elective single embryo transfer rate					X			
Clinical pregnancy rate						X		
Multiple pregnancy rate						X		
Miscarriage rate							X	
Live birth rate								X
Stillbirth rate								X
Multiple birth rate								X
Serious adverse events			X		X	X	X	X

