#### Notification and reporting of serious adverse events

Data on SAEs will be documented from randomisation, at the scheduled outcome assessment points from the medical records, and up to 6 weeks post-delivery in case of successful pregnancies. This may include telephone contact with the mother approximately 6 weeks after delivery if required. Research staff should refer to all available resources including medical records, online systems such as CRS, and discussions with participants themselves to ensure that all reportable SAEs are elicited.

Any SAEs that require reporting need to be reported by the local PI to the chief investigator (CI) within 24 h of learning of the event. The CI will assess the event and can always upgrade the relationship or severity of the event, but never downgrade it. The CI will assess if a ‘related’ SAE was ‘unexpected’. Serious adverse events (SAEs) that are considered to be ‘related’ and ‘unexpected’ are then to be reported to the sponsor within 24 h of learning of the event and to the Research Ethics Committee (REC) within 15 days in line with the required timeframe. International sites will report to the QMUL sponsor in addition to their own sponsor.

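### Allocation may be released on request at the end of pregnancy, while serious adverse events are still collected, partly from the mother, for about six weeks after delivery

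*Protocol article*

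**What the plan says.** Two sets of statements in the protocol article bear on this.

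**When participation and blinding end.** Study design follows women either to a negative test or "to the end of their pregnancy following a positive pregnancy test". Who will be blinded {17a} states: "Participants will be blinded to the allocated intervention until the end of their participation in the trial", and then defines that end: "This will either be a negative pregnancy test which is approximately 2 weeks after embryo transfer or the end of their pregnancy". Procedure for unblinding if needed {17b} adds that "participants may request to be informed of their allocation when they reach the end of their study participation", naming unsuccessful pregnancy and the end of pregnancy as the two occasions. It gives one instruction for such releases: "Care will be taken not to disclose the allocation to any other member of the research team". It also has any unblinding reported to the Data Monitoring Committee (DMC) and in the final report.

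**When data collection ends.** Notification and reporting of serious adverse events runs SAE documentation from randomisation "up to 6 weeks post-delivery in case of successful pregnancies. This may include telephone contact with the mother approximately 6 weeks after delivery"; the sentence goes on to make that call conditional on need. The same section lists discussions with participants among the sources for finding SAEs. The last column of Table 1 (Participant timeline {13}) is headed "Approx. 6 weeks after the expected due date" and holds live birth, stillbirth, multiple birth and SAEs. Plans for assessment and collection of outcomes {18a} has research staff telephone participants when outcome data are missing from the records.

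**The concern.** The stated end of participation falls before the last data collection. Between the two, a woman who has delivered may learn her arm and still be asked about events in herself or her baby.

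Two kinds of data could be affected. The first is the reporting of SAEs after delivery. A mother who knows which incubation her embryos had may mention, or look for, events differently. The second is the relatedness judgement. The local investigator decides whether an SAE is related to trial procedures, and any event judged related to a time-lapse device is automatically unexpected. Related and unexpected events go to the sponsor within 24 hours, to the ethics committee within 15 days, and to the DMC for review. Only the two intervention arms use the device, so an arm disclosed by the mother bears directly on that judgement.

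The protocol itself says that the long-term safety of the procedure is unknown, so the safety data deserve protection where this costs little.

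**Working it through.** The protocol states no figure on this point, so the check is mainly a comparison of timings.

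**1. Timeline for a woman who delivers.**
- Delivery: participation ends (Study design, {17a}) and allocation may be given on request ({17b}).
- Delivery + 6 weeks: SAE collection closes (Notification and reporting of serious adverse events).
- Expected due date + about 6 weeks: last SAE and outcome assessment (Table 1).

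Under the SAE section the gap is up to 6 weeks. Under Table 1 it depends on when she delivers. With an assumed due date at 40 weeks, delivery at 40 weeks gives 6 weeks, and delivery at 32 weeks gives (40 − 32) + 6 = 14 weeks. The two sections therefore give different closing dates whenever delivery is not on the due date.

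**2. Which data can still change after delivery.**
- Live birth, stillbirth, multiple birth, birth weight and gestational age are settled at delivery. Table 1 shows when some of them are recorded; a mother's later knowledge does not alter them.
- The specific rule on congenital anomalies covers those identified at birth or earlier. An anomaly found later comes in through the general SAE window.
- Admissions to neonatal intensive care (NICU) are reportable SAEs except for the listed events (low or very low birth weight, small or large for gestational age, preterm or very preterm delivery).
- What stays open is therefore post-delivery SAEs, including later-detected anomalies and the reportable NICU admissions, together with their assessed relatedness.

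**3. Who could be influenced.** {17a} leaves embryologists unblinded and the trial statistician semi-blinded, and blinds all other local and central staff. The instruction in {17b} concerns the release of the code to other members of the team. Nothing asks the participant to keep her allocation to herself when blinded staff contact her.

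**4. Outer limit on numbers.** From Sample size {14}: 525 randomisations per arm, with live birth rates of 26.5% and 35.25%.
- 525 × 0.265 = 139.1, about 139.
- 525 × 0.3525 = 185.1, about 185.

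These are expected live births per arm. The affected group is the subset of women who ask for their allocation, are then contacted or consulted, and have a reportable event whose reporting or assessment turns on what they say. The documents give none of these proportions.

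**The case against.** The best defence is that harm needs a chain of steps. The woman must ask and be told; she must then be contacted although records are the main source and the call is made only if required; she must disclose her arm or report differently because of it; and the investigator's judgement must shift. Follow-up is described as part of standard care because of regulatory reporting. Relatedness is judged by a blinded investigator rather than by the mother, and the chief investigator may upgrade that judgement. Every unblinding also reaches the DMC and the final report.

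Much of this stands, and it limits the weight of the point. It does not remove it. Reporting an unblinding documents it but does not prevent bias. The chief investigator can upgrade relatedness or severity but never downgrade it, so only an under-call can be corrected. The instruction on disclosure does not reach the mother.

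A reader might infer more than the text supports, in four ways:
- **That the primary result is at risk.** Live birth is fixed before allocation can be released on this ground.
- **That 139 to 185 women per arm are affected.** Those are simply the expected live births.
- **That these SAEs are the only safety data on the baby.** Birth weight, gestational age and stillbirth are separate safety outcomes, and neonatal data are collected.
- **That most NICU admissions are SAEs.** The exceptions are substantial, and the documents give no figures from which to say so.

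**Conclusion.** The inconsistency is real. The sections that end participation and blinding at the end of pregnancy do not fit the sections that collect data for about six weeks more. The effect is an avoidable route to bias in post-delivery SAE reporting and in the relatedness judgement.

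The importance is minor to moderate. The primary outcome and the birth outcomes fixed at delivery are unaffected. The size of any bias cannot be derived from the documents. The conclusion assumes only that some women ask for their allocation soon after delivery and that some of them are later consulted about SAEs; the protocol permits both.

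**What to change.** - In Study design, {17a} and {17b}, define the end of participation for women who deliver as completion of the final post-delivery SAE and outcome collection. Release allocation on request only once that form is complete.
- Reconcile the two closing dates, six weeks after delivery (SAE section) and about six weeks after the expected due date (Table 1), so that the release point is unambiguous.
- Leave emergency unblinding and release after a negative pregnancy test as they are.

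The cost is a wording change and a note to the embryologists who hold the code. No visits, data items or sample size are added. Women who ask wait about six weeks longer, or more after a preterm delivery if the due-date anchor is kept.

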## Data collection and management

### Plans for assessment and collection of outcomes {18a}

Trial data will be recorded by the research team at each of the participating centres directly onto trial-specific secure password-protected electronic case report forms (eCRFs) in a database administered by epiGenesys, University of Sheffield. Data that is entered directly by the embryologists (randomisation data and intervention data) will be restricted to allow access only to unblinded staff members.

The following data will be collected:
Baseline demographic data (age, ethnicity)Baseline clinical data (category of infertility, type of infertility, duration of infertility, BMI, treatment attempt, parameters of egg reserve and sperm count)Clinical treatment data (stimulation protocol, drug dosages, duration of stimulation, number of oocytes retrieved, type of insemination procedure, number of embryos available, fresh/frozen transfer, day of embryo transfer, number of embryos transferred and type of time-lapse machine, embryo grading; if applicable, documentation of morphokinetic parameters will be documented and submitted separately by embryologists to maintain blinding of the remaining study team)Data for all clinical outcomes (live birth, pregnancy test outcome, implantation, clinical pregnancy, multiple pregnancy, miscarriage, stillbirth, neonatal data)

For all participants, clinical and laboratory data are routinely recorded in the fertility medical notes or fertility electronic database by clinical staff. If clinical outcome data are not available in the medical records, a trained delegated member of the research team will phone the participants to obtain this data. Trained and delegated members of the trial team, as documented on the trial delegation log, will be responsible for the completion of the eCRFs.

### Plans to promote participant retention and complete follow-up {18b}

If consent is withdrawn, data already collected up to the point of withdrawal will be retained, and permission will be sought to complete follow-up outcomes data collection. The duration of the intervention is short, and follow-up procedures are part of standard care due to HFEA reporting requirements; hence, we do not anticipate issues with follow-up.

### Data management {19}

All data management will be undertaken by the Queen Mary University of London. Standard operating procedures will be in place for the collection and handling of data received at the centre. All study data will be entered into a secure, bespoke electronic trial database with restricted access. Data collected on the data collection forms and entered onto the electronic database will only identify the participants by a unique trial number.

Data will be processed on a workstation by authorised staff. The workstations access the network via a login name and password. No data are stored on individual workstations. Backing up is done automatically overnight to an off-site storage area. Sites will allow access to source data and documentation for the purpose of monitoring, auditing and inspections, for the relevant authorised individuals.

### Confidentiality {27}

The investigator has a responsibility to ensure that patient anonymity is protected and maintained. They must also ensure that their identities are protected from any unauthorised parties. Information with regard to the study patients from UK sites will be kept confidential and managed in accordance with the Data Protection Act (2018), NHS Caldecott Guardian, principles, The Research Governance Framework for Health and Social Care, and Research Ethics Committee Approval. International sites will abide by their own countries regulatory requirements.

The trial will collect personal data and sensitive information about the participants either directly or from their clinical team. Participants will be informed about the transfer of this information to the study office and will be asked to consent to this. The data will be entered onto a secure computer database, either by trials unit staff or directly via a secure internet connection. Any data to be processed will be pseudo-anonymised. At recruitment, eCRFs will be pseudonymised using a unique participant code that is allocated by the recruiting member of staff. At randomisation, an additional unique code will be generated by the online randomisation system and recorded on the randomisation form. All personal information obtained for the trial will be held securely and treated as strictly confidential. All staff, at each hospital and the trials unit, share the same duty of care to prevent unauthorised disclosure of personal information. No data that could be used to identify an individual will be published. The chief investigator, [name], is the ‘custodian’ of the data.

### Plans for collection, laboratory evaluation and storage of biological specimens for genetic or molecular analysis in this trial/future use {33}

Not applicable as no biological specimens will be collected as a part of this trial.

## Statistical methods

### Statistical methods for primary and secondary outcomes {20a}

Analyses will be intention-to-treat, will include all randomised participants and will analyse according to the treatment group to which they were randomised. We will analyse each participant randomisation as an independent observation (i.e. perform an independence analysis). As a sensitivity analysis, we will provide results from analyses restricted to complete cases, for comparison with results based on multiple imputation.

For each analysis, we will present the treatment effect (difference in means for a continuous outcome and an odds ratio for binary outcomes) along with a 95% confidence interval and a two-sided *p* value. Because we have two main treatment comparisons (TLI vs. standard care, and undisturbed culture vs. standard care), the significance level for the primary outcome is set at 2.5% for each treatment comparison. The primary outcome (live birth) will be analysed using logistic regression model and will be adjusted for stratification and minimisation factors and other pre-specified covariates to increase power. The stratification factor is the fertility clinic and the minimisation factors are participant’s age (< 35 years, 35–40 years, > 40 years) and type of planned first embryo transfer (fresh, frozen). Other covariates to be included in the analyses are treatment attempt, type of infertility (primary/secondary), category of infertility, duration of infertility, BMI, type of time-lapse imaging equipment, method of insemination (IVF vs. ICSI), number of retrieved oocytes and number of available embryos. A full statistical analysis plan will be developed and finalised prior to data analysis and will include full specifications on subgroup analyses.

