### Sample size {14}

#### Sample size

The sample size calculation was based upon the primary outcome of live birth. With a 5% overall significance level (2.5% for each of the two main treatment comparisons: TLI vs. standard care, and undisturbed culture vs. standard care), we would require 514 participant randomisations per treatment arm to detect an absolute increase in the primary outcome from 26.5 to 35.25% with 80% power. Allowing for 2% loss to follow-up or withdrawal of consent would require 525 participants per treatment arm (1575 in total).

The comparison between experimental treatment arms (TLI vs. undisturbed culture) will be performed with no impact on sample size because we will carry out this statistical test conditional to the rejection of at least one of the primary comparisons planned (TLI vs. standard care, or undisturbed culture vs. standard care). This hierarchical approach permits to maintain the overall type I error rate of 5%.

This trial uses the re-randomisation design, which was described by Kahan et al. [9]. Requirements for the re-randomisation design are as follows:
Patients are only re-randomised when they have completed the follow-up period from their previous randomisation.Randomisations for the same patient are performed independently.The treatment effect is constant across all randomisation periods.

Requirement 1 is fully satisfied, as participants will have completed their previous round of treatment before re-joining the study. Participants have an equal chance of being randomised to either of the three trial arms, regardless of their previous randomisation result, therefore satisfying requirement 2. Finally, there is no anticipated treatment effect, either in terms of efficacy or safety, from one episode to the next.

It has been demonstrated that introducing re-randomisation in a trial will not affect the validity of the statistical analysis and results [9].

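### The two primary live-birth comparisons are tested at two-sided 2.5% but reported with 95% confidence intervals, so interval and test point different ways whenever p lies between 0.025 and 0.05

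*Protocol article*

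**What the plan says.** The section on statistical methods for primary and secondary outcomes {20a} sets the reporting rule and the test level in consecutive sentences.

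- Reporting rule: "For each analysis, we will present the treatment effect", with a difference in means for continuous outcomes and "an odds ratio for binary outcomes) along with a 95% confidence interval". The interval is paired with a two-sided p value. No exception is made for the primary outcome.
- Test level: "the significance level for the primary outcome is set at 2.5% for each treatment comparison".

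The sample size section {14} gives the same split: "With a 5% overall significance level (2.5% for each of the two main treatment comparisons". It claims a 5% overall type I error rate. It also makes the test of TLI against undisturbed culture conditional on rejecting at least one of the two primary comparisons.

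The article nowhere gives a 97.5% or otherwise adjusted interval for live birth. It does not call the 95% interval descriptive, and it does not say that significance is judged by the p value alone.

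**The concern.** A two-sided confidence interval and a two-sided test agree only when the confidence level is one minus the test level. Here the test level is 2.5% and the interval level is 95%, which leaves a band of results where the primary table would say two things: an interval for the odds ratio that lies wholly above (or below) 1, and a test that the plan counts as not significant.

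This matters because many readers judge a result by its interval. The dissemination plans {31a} name the NICE guideline process, the Cochrane review and NHS commissioners as users of the findings. A reader who sees a 95% interval excluding 1 could also think that the condition for testing TLI against undisturbed culture has been met when it has not.

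**Working it through.** **Inputs.** From the sample size section: live birth 26.5% vs 35.25%, 80% power, 5% overall and 2.5% per comparison, 514 per arm, 525 per arm (1575 in total) after 2% loss. From the statistical methods section: 95% interval and two-sided p value. From the trial design section: 1:1:1 allocation.

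**1. Which level was the trial sized at?** With z(0.9875) = 2.2414, z(0.80) = 0.8416 and mean proportion 0.30875, the pooled-variance formula is

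n = [2.2414 × √(2 × 0.30875 × 0.69125) + 0.8416 × √(0.265 × 0.735 + 0.3525 × 0.6475)]² / 0.0875² = 529 per arm.

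The unpooled version gives 526. The stated 514 is 2.8% and 2.3% below these, and its power at two-sided 2.5% is 78.8%, close to the planned 80%. At two-sided 5% the pooled formula gives only 437. The trial was therefore sized at 2.5% per comparison. The allowance for loss also reproduces: 514 / 0.98 = 524.5, rounded up to 525, and 3 × 525 = 1575.

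**2. Where interval and test part.** The 95% interval excludes an odds ratio of 1 when |z| > 1.960 (p < 0.05). The plan's test rejects when |z| > 2.241 (p < 0.025). They disagree for 0.025 <= p < 0.05.

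**3. How often, per comparison.**

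- No effect: 0.05 − 0.025 = 2.5% of trials.
- Design effect, 514 per arm: power at 5% minus power at 2.5% = 86.0% − 78.8% = 7.2% of trials.

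**4. An illustration (unadjusted, 514 per arm).** Take 136 live births under standard care (26.5%) and 167 in an intervention arm (32.5%).

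- Log odds ratio = ln(167/347) − ln(136/378) = 0.291, so OR = 1.34.
- SE = √(1/167 + 1/347 + 1/136 + 1/378) = 0.137; z = 2.12; p = 0.034.
- 95% interval: 1.02 to 1.75, which excludes 1.
- 97.5% interval: 0.98 to 1.82, which includes 1.

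With 136 events under standard care, every count from 165 (p = 0.047) to 168 (p = 0.029) falls in this band. At 169 (p = 0.0245) the test rejects and the 97.5% interval (1.001 to 1.85) also excludes 1.

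**5. Familywise error over the two primary comparisons.** Equal arms with a shared control give a correlation of 0.5 between the two test statistics under the global null. The chance that at least one |z| exceeds c is

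1 − ∫ φ(u) [Φ((c − √0.5 u)/√0.5) − Φ((−c − √0.5 u)/√0.5)]² du.

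| Critical value | Chance of at least one exceedance | Bonferroni bound |
|---|---|---|
| 2.241 (the plan's test) | 4.6% | 5% |
| 1.960 (95% intervals read as tests) | 9.1% | 10% |

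**6. Effect on interval width.** 2.2414 / 1.9600 = 1.144, so a 97.5% interval is about 14% wider on the log-odds scale.

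**The case against.** The strongest reply is that there is only one decision rule. The 2.5% level is stated plainly in two sections, and the 95% interval appears only in a sentence about what will be presented. The p value will stand beside the interval, so a reader who knows the threshold is not misled. Marginal 95% intervals beside a Bonferroni-adjusted test are an accepted reporting convention, and each keeps its own 95% coverage. Anyone can obtain the 97.5% interval by stretching the published one by a factor of 1.144 on the log scale.

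Much of this stands. A reader might infer from the mismatch that the trial's type I error control is lost, or that its true error rate is 9.1%. The document does not support that. The 5% control is claimed for the tests, which deliver it, and simultaneous coverage of the intervals is never claimed. The 9.1% applies only to someone who uses the 95% intervals as tests.

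What does not stand is that the text already settles the matter. It fixes 95% for each analysis, the primary one included, without calling that interval descriptive. The full analysis plan is promised but not shown. If it follows this sentence it inherits the mismatch, and if it uses another level it departs from the protocol.

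**Conclusion.** The point holds as a moderate reporting fault: the intervals prescribed for the two primary comparisons do not match the rule by which those comparisons are decided. The tests, the sample size and the model are not affected, so it would be wrong to treat this as a flaw that invalidates the analysis.

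The 7.2% assumes that the true rates are exactly 26.5% and 35.25%, with 514 evaluable randomisations per arm and an unadjusted normal-approximation comparison. The share differs for other effects, and covariate adjustment or multiple imputation would shift it somewhat. The 4.6% and 9.1% assume equal arm sizes and independent randomisations, as the plan's independence analysis does. The mismatch itself needs none of these assumptions, because it follows from the two stated levels. Secondary outcomes are not touched, since the 2.5% level is set only for the primary outcome.

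**What to change.** Amend the reporting sentence in the statistical methods section, and carry it into the analysis plan before any comparison by arm is seen:

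- For live birth, TLI vs standard care and undisturbed culture vs standard care, report the odds ratio with a 97.5% confidence interval and a two-sided p value, and state that significance is judged at p < 0.025.
- If 95% intervals are also wanted for comparison with other trials, show them beside the 97.5% intervals, labelled as not adjusted for multiplicity.
- Keep 95% intervals for secondary outcomes.

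The cost is a sentence or two of text and a primary interval about 14% wider on the log-odds scale. The sample size, data collection and model stay as they are. A smaller change, which only states that p < 0.025 decides and that the 95% interval is descriptive, would remove the ambiguity but leave the primary table without an interval that matches the test.
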